### Sample size calculations

No previous study has evaluated the effect of a DPP4 inhibitor on cisplatin-induced AKI. We expect that the incidence of AKI will be 25 % in patients treated with a single dose of cisplatin and that treatment with a DPP4 inhibitor could reduce this incidence by 60 %. We calculated the required sample size for an estimated dropout rate of 20 %, a one-sided level of significance of α = 5 %, and a power of 80 % and found that 91 participants will be needed in each group to find a significant difference using a *χ*^2^ test. A total of 182 participants will be included in the analysis.

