### Statistical analyses

Statistical analyses will be conducted on both per protocol (PP) and intention-to treat (ITT) bases. For the PP analysis, all participants who completed the study will be included to evaluate the primary and secondary outcomes. For the ITT analysis, all participants who were enrolled and randomized to one of the two groups will be included.

The baseline characteristics and laboratory data will be presented as the means and standard deviations for continuous variables and as frequencies and percentages for categorical variables. The incidence of AKI will be compared between the two groups using a *χ*^2^ test. The differences in changes in SCr levels and in the eGFR will be analyzed using Student’s *t*-test or the Mann-Whitney *U* test. A value of *P* < 0.05 will be considered statistically significant. All analyses will be performed using SPSS Statistics software V21.0 (IBM Corporation, Armonk, NY, USA).

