## Discussion

Cisplatin is an effective anti-tumor drug whose clinical application is limited by its nephrotoxicity [1, 8]. Conventional renoprotective measures in patients receiving cisplatin are not satisfactory. Many studies have investigated the effects of protective strategies targeting the molecular mechanisms of cisplatin toxicity. Although encouraging results have been found in *in vitro* and *in vivo* models, a lack of positive data in clinical trials has prevented the effective clinical application of these strategies [1, 15, 16]. DPP4 inhibitors, which are anti-diabetic drugs, have been shown to protect various organs from injuries [19–29]. This trial is the first to investigate whether a DPP4 inhibitor protects the kidney from cisplatin-induced injury in humans.

Previous studies have reported that cisplatin-induced AKI occurred in 6–35 % of patients within 7 days after a single dose of cisplatin [1, 5, 6, 31] and resolved within 15 days [7]. The incidence of AKI in patients treated with a single dose of cisplatin was 14.4 % at our institution. The average follow-up time was 17 days. However, the incidence of AKI would be higher than 14.4 % if we considered renal function within 7 days after cisplatin treatment; we estimate that the incidence of AKI would be approximately 25 %. We tentatively suggest that treatment with a DPP4 inhibitor could result in a 60 % reduction in the risk of AKI. The statistical power may be compromised if sample size is calculated using a one-sided level instead of a two-sided level. However, this trial is a phase II exploratory research, not a phase III or IV study on the possibility of direct clinical application. In addition, from the previous study [29], it is expected that DPP4 inhibitors will ameliorate rather than have no impact on or exacerbate cisplatin-induced AKI. It is not feasible to enroll more participants in our institution even though this study will be extended. Nevertheless, based on our assumptions, the sample size required for this study is larger than that of previous clinical studies of cisplatin-induced nephrotoxicity [15, 34–38].

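### The sample size assumes a one-sided 5% test, but the analysis section sets P < 0.05 on a chi-square test without a direction; read as two-sided, power is about 76% with all 182 analysed and about 67% after the planned dropout, not 80%

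*Protocol article*

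**What the plan says.** All three places are in the protocol article.

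- **Sample size calculations** uses "a one-sided level of significance of α = 5" per cent, "and a power of 80" per cent and a chi-square test. The control incidence is set by "We expect that the incidence of AKI will be 25" per cent, and treatment "could reduce this incidence by 60" per cent, which gives 10% on gemigliptin. Allowing "for an estimated dropout rate of 20" per cent, it arrives at 91 per group, and it says that all 182 will enter the analysis.
- **Statistical analyses** names a chi-square test for AKI incidence and adds "A value of *P* < 0.05 will be considered statistically significant". It does not say one-sided or two-sided and gives no directional rule. It plans both an intention-to-treat analysis of everyone randomised and a per-protocol analysis of completers.
- **Discussion** says "The statistical power may be compromised if sample size is calculated using a one-sided level instead of a two-sided level". It justifies the choice on three grounds: the trial is exploratory phase II research, benefit is the expected direction, and the centre cannot enrol more participants.

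**The concern.** The Pearson chi-square statistic squares the difference between arms, so its P value takes no account of direction. Rejecting at P < 0.05 puts about 2.5% of the error on each side. A one-sided 5% rule puts the whole 5% on the side of benefit. These are different decision rules, and the protocol does not say which one decides the primary outcome.

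Two things are at stake. First, the stated 80% power belongs to the one-sided rule; if the undirected rule is the one applied, the trial has less. Second, any result in favour of gemigliptin with a two-sided P between 0.05 and 0.10 is positive under one rule and negative under the other. With neither named, the choice could be made after the data are seen.

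**Working it through.** **Inputs** (Sample size calculations): p1 = 0.25; p2 = 0.25 × (1 − 0.60) = 0.10; difference 0.15; 91 per arm; 20% dropout, so 91 × 0.80 = 72.8, about 73 evaluable per arm. Normal quantiles: 1.6449 (one-sided 5%), 1.9600 (two-sided 5%), 0.8416 (80% power).

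**Step 1: reproduce 91.** With unpooled variance, n = (1.6449 + 0.8416)² × (0.25 × 0.75 + 0.10 × 0.90) / 0.15² = 6.183 × 0.2775 / 0.0225 = 76.25. Then 76 × 1.2 = 91.2, which matches 91. The match needs dropout to be added as n × 1.2; dividing by 0.8 gives 96. Two-sided versions that allow for dropout need 116 to 142 per arm, so the 91 is a one-sided figure.

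**Step 2: power of the uncorrected chi-square test.** Power = Φ[(0.15√n − z × s0) / s1], with s0 = √(2 × 0.175 × 0.825) = 0.5374 and s1 = √0.2775 = 0.5268.

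- n = 73, one-sided: (1.2816 − 0.8839) / 0.5268 = 0.755, power 77.5%
- n = 73, two-sided: (1.2816 − 1.0532) / 0.5268 = 0.434, power 66.8%
- n = 91, one-sided: (1.4309 − 0.8839) / 0.5268 = 1.038, power 85.0%
- n = 91, two-sided: (1.4309 − 1.0532) / 0.5268 = 0.717, power 76.3%

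Exact binomial enumeration gives 78.9%, 68.2%, 85.7% and 77.2% in the same order.

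**Step 3: separate the causes.** Sidedness costs 85.0 − 76.3 = 8.7 points at 91 per arm and 77.5 − 66.8 = 10.7 points at 73. The other 80 − 77.5 = 2.5 points at 73 per arm are not due to sidedness. They arise because 76 × 1.2 leaves only 73 after a 20% loss, where division by 0.8 would have kept the evaluable number intact. The formula in step 2 gives 78.9% one-sided at 76 per arm, so about 1.5 of the 2.5 points come from the inflation itself. About 1 point comes from sizing with unpooled variance while power is computed here with pooled variance.

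**Step 4: size needed for 80% two-sided.** n = [(1.9600 × 0.5374 + 0.8416 × 0.5268) / 0.15]² = 99.5, so 100 evaluable per arm, or 100 / 0.8 = 125 randomised per arm.

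**Step 5: results on which the rules disagree.** With 23/91 control events, 13/91 treated events give chi-square P = 0.063 and 14/91 give 0.097. With 18/73 control events, 9/73 give 0.055 and 10/73 give 0.093. All four are negative at an undirected P < 0.05 and positive one-sided at 5%.

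**The case against.** The strongest reply is that the protocol has already chosen. The sample size section puts one-sided and chi-square in the same sentence, the stated hypothesis is directional, and the Discussion discusses the one-sided choice openly. On that view the analysis section simply carries the one-sided rule forward. This stands in part: the analysis section never says two-sided, so that reading is an inference from the test and the unqualified threshold. But it is the ordinary reading of a chi-square P value, and nothing in the analysis section tells the analyst to depart from it.

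The Discussion's three grounds also deserve their weight. Exploratory phase II status is a usual reason for a one-sided level. They could justify running a one-sided test. They do not justify powering one test and leaving open which one is run.

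A reader might go further and infer that the true power is simply 67% because of sidedness. The documents do not support that. The 67% applies only if the 20% dropouts leave the analysis, whereas both the sample size section and the intention-to-treat definition speak of analysing everyone. Even at 73 per arm, one-sided power is already 77.5%. Nor is the choice concealed: the one-sided level and its effect on power are both on the page.

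**Conclusion.** The point holds in this form: the level used for sizing is one-sided, the level at analysis has no stated side, and the stated 80% is not met if the usual two-sided reading applies. Two-sided power is about 76% with all 182 analysed and about 67% with 73 evaluable per arm, against about 85% and 77.5% one-sided. Sidedness accounts for 9 to 11 points. The Discussion discloses a loss of power but neither quantifies it nor settles which rule governs.

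The figures rest on the protocol's own 25% and 10%, equal arms and a chi-square test without continuity correction. The 76% also assumes that every randomised participant has an outcome and that the same incidences hold among those who drop out.

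**What to change.** Before unblinding, name the sidedness of the primary test in Statistical analyses and give the matching power in Sample size calculations. Either of two versions would do:

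- **Two-sided 5%**, with power restated as about 76% if all 182 are analysed and about 67% with 73 evaluable per arm.
- **One-sided 5%**, written out as rejecting only for a lower AKI incidence on gemigliptin, reported with a 90% confidence interval, and with power restated as about 85% and about 77.5%.

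The Discussion sentence on power should then carry the chosen figures. The cost is wording in two paragraphs and that sentence, with no extra patients. The downside is a less favourable power statement under the two-sided version. The one-sided version keeps a 5% false-positive rate in the direction of benefit, which should be stated alongside the result.

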### Ethical approval

The study will be performed in accordance with the Declaration of Helsinki, as amended by the 64th World Medical Association General Assembly in 2013. All of the participants will provide written, informed consent stating that participation is voluntary and can be withdrawn at any time. This study was approved by the Institutional Review Board of the Seoul National University Bundang Hospital (B-1408/264-002). The trial protocol has been registered at http://www.clinicaltrials.gov (NCT02250872).

## Discussion

Cisplatin is an effective anti-tumor drug whose clinical application is limited by its nephrotoxicity [1, 8]. Conventional renoprotective measures in patients receiving cisplatin are not satisfactory. Many studies have investigated the effects of protective strategies targeting the molecular mechanisms of cisplatin toxicity. Although encouraging results have been found in *in vitro* and *in vivo* models, a lack of positive data in clinical trials has prevented the effective clinical application of these strategies [1, 15, 16]. DPP4 inhibitors, which are anti-diabetic drugs, have been shown to protect various organs from injuries [19–29]. This trial is the first to investigate whether a DPP4 inhibitor protects the kidney from cisplatin-induced injury in humans.

Previous studies have reported that cisplatin-induced AKI occurred in 6–35 % of patients within 7 days after a single dose of cisplatin [1, 5, 6, 31] and resolved within 15 days [7]. The incidence of AKI in patients treated with a single dose of cisplatin was 14.4 % at our institution. The average follow-up time was 17 days. However, the incidence of AKI would be higher than 14.4 % if we considered renal function within 7 days after cisplatin treatment; we estimate that the incidence of AKI would be approximately 25 %. We tentatively suggest that treatment with a DPP4 inhibitor could result in a 60 % reduction in the risk of AKI. The statistical power may be compromised if sample size is calculated using a one-sided level instead of a two-sided level. However, this trial is a phase II exploratory research, not a phase III or IV study on the possibility of direct clinical application. In addition, from the previous study [29], it is expected that DPP4 inhibitors will ameliorate rather than have no impact on or exacerbate cisplatin-induced AKI. It is not feasible to enroll more participants in our institution even though this study will be extended. Nevertheless, based on our assumptions, the sample size required for this study is larger than that of previous clinical studies of cisplatin-induced nephrotoxicity [15, 34–38].

We have considered the potential interactions between gemigliptin and cisplatin from the beginning of this study. First, cisplatin has no effect on hepatic cytochrome P450 3A4 (CYP3A4) in human liver microsomes [39], while gemigliptin is largely metabolized by CYP3A4 [40]. Second, cisplatin is mainly excreted by the kidney, and its nephrotoxicity is mediated via organic cation transporter 2 (OCT2) in the kidney [1, 41]. Gemigliptin and its active metabolite, LC15-0636, are very weak inhibitors of OCT2 in cultured xenopus oocytes. In terms of metabolic pathways and the renal transport system, cisplatin and gemigliptin never interact. Therefore, the renoprotective effect of gemigliptin could be investigated without affecting the anti-tumor activity of cisplatin.

The dose of gemigliptin in this study is two times higher than the dose used in the treatment of diabetes. Based on previous studies [29, 42], we determined that this dose was necessary to inhibit DPP4 activity by more than 80 % during cisplatin exposure.

DPP4 inhibition has not caused hypoglycemia in studies of healthy volunteers [43, 44]. Because the effects of GLP-1 on insulin secretion are glucose-dependent, the risk of hypoglycemia associated with DPP4 inhibitor treatment is low [45]. Nonetheless, we will exclude the participants with diabetes from this study. Therefore, the risk of hypoglycemia due to gemigliptin administration may be almost negligible in this trial.

A strength of this trial is that we will standardize hydration protocols before, during, and after cisplatin treatment to minimize the effects of confounding variables associated with renal outcomes. Cisplatin dosage per body surface area and the presence of diabetes have been reported to be the risk factors for moderate and severe cisplatin-induced AKI [31]. Another strength of this study is that randomization will be stratified on the basis of cisplatin dosage. Furthermore, participants with diabetes will be excluded from this study.

A small number of trials have investigated the clinical use of DPP4 inhibitors in the treatment of conditions other than diabetes. Treatments with DPP4 inhibitors have been investigated for their ability to enhance engraftment following umbilical cord blood transplantation in adults with hematologic malignancies [46], to improve endothelial dysfunction, and to prevent major cardiovascular events in patients with type 2 diabetes [47–49]. Again, we emphasize the originality of this trial, which will investigate the effect of a DPP4 inhibitor on cisplatin-induced AKI.

A limitation of this study is the diversity among the study participants and chemotherapeutic agents. Patients with different types of cancer receiving various anticancer drugs will be enrolled in this study. We expect that patients with gastric, biliary, head and neck, and lung cancer will be enrolled in this study. The following chemotherapeutic agents are used together with cisplatin in the treatment of these cancers: capecitabine, tegafur, docetaxel, pemetrexed, etoposide, irinotecan, and gemcitabine. All of these agents have been reported to have a low risk of AKI [50].

In summary, the present study is the first prospective, randomized controlled trial to evaluate the effect of a DPP4 inhibitor on cisplatin-induced AKI. The aim of this study is to demonstrate whether treatment with a DPP4 inhibitor, gemigliptin, can reduce the incidence of cisplatin-induced AKI in patients receiving cisplatin.

### Trial status

This trial is ongoing. Participants are currently being recruited.

## Abbreviations

AKI: Acute kidney injury
DPP4: Dipeptidyl peptidase-4
GLP-1: Glucagon-like peptide-1
NSAID: Nonsteroidal anti-inflammatory drug
SCr: Serum creatinine
eGFR: Estimated glomerular filtration rate
PP: Per protocol
ITT: Intention-to treat
CYP3A4: Cytochrome P450 3A4
OCT2: Organic cation transporter
